#### Step 3 active dissemination: information support group intervention

Initial analyses will use demographic data to compare the characteristics of participants who agree to participate in Step 3 compared to those who decline to participate in this step of the project (despite meeting eligibility criteria, i.e. K10 > 15). Differences in responses according to demographic variables on the construct measures of interest (K10, FAD, family belief systems and MOSSSS) will also be analysed using oneway ANOVAs.

To examine the additional impact of the information support group intervention, relative to the wait-list control group (who will have only received the booklet intervention), an analysis of covariance will examine changes in mean scores on the outcome measures from baseline to post-intervention follow-up according to Group (n ≈ 60) versus Waitlist (n ≈ 60) allocation. To account for participant deviations from the protocol (such as dropout or failure to sufficiently participate in the group intervention), two analyses will be conducted. Data will be analysed using the intention-to-treat principle, which will assume all participants randomised to the intervention or waitlist group completed the study as per the research design and a per-protocol analysis will include only those participants who participate in a minimum of two-thirds of the intervention (Porta et al. 2007). Following post-intervention follow-up data collection, the waitlist group will complete the information support group intervention, and complete the post-intervention follow up. All group-based intervention participants will complete a six-month follow-up assessment. Thus, to test for sustained change, a second analysis will compare mean scores at baseline, post-intervention and six-month follow up on the same outcome measures for all participants in Step 3 of the intervention (n ≈ 120). There will be no treatment allocation variable in this second analysis. Further analyses will adjust for baseline characteristics to control for any confounding effects.

Additional analyses will identify risk and protective factors on each construct measure (for example, scoring above 15 on the K10) (Slade et al. 2011) at baseline for Group and Waitlist participants, and include comparisons for participants who agree to participate in Step 3 of the intervention and attend the Information Support group, compared to those who decline to participate in this step of the project, despite meeting eligibility criteria.

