#### Step 3 active dissemination: parent information support group intervention

The data from the three-month follow-up assessment for Step 2 will constitute the baseline (or pre-group) data for Step 3. Participants in Step 3 will also complete an additional questionnaire at the first group session regarding their expectations of the group and what mental health support they might already be receiving. Medical records for the child of parents in Step 3 will be reviewed to record any hospital-based nursing or allied health staff involvement with the family.

On completion of the Information Support group, participants will be provided with the follow up questionnaire as part of the last group session. Follow up assessment of the group intervention will occur between April – September 2014. Participants in the waitlist control group will be completing the 6-month follow up assessment from baseline in Step 2 of the study at this time. This will provide the control comparison data to assess the additional impact of the group intervention, compared to receiving the booklet alone. The waitlist control group will then proceed to participate in the group intervention. All participants in Step 3 will be scheduled to complete a final follow up (single-group) assessment six months after they attended the group. This will provide repeated measures pre-post data regarding the longer-term efficacy of the group intervention. Participants will receive a prompt letter regarding six month follow up and approximately two weeks later a phone call, giving them the option to complete the questionnaire over the phone, online or receive a hard copy in the mail. Six-month follow up of participants in Step 3 is anticipated to occur between October 2014 – March 2015.

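### Step 3 describes intention-to-treat as assumed completion, and its two-thirds per-protocol rule cannot be applied to the waitlist arm, so the per-protocol contrast is not a randomised comparison

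*Protocol article*

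**What the plan says.** Under Statistical analyses, Step 3, the protocol article plans an analysis of covariance of the outcome measures by allocation, about 60 group parents against about 60 waitlist parents. It then says: "To account for participant deviations from the protocol (such as dropout or failure to sufficiently participate in the group intervention), two analyses will be conducted".

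- The first follows the intention-to-treat principle, "which will assume all participants randomised to the intervention or waitlist group completed the study as per the research design".
- In the second, "a per-protocol analysis will include only those participants who participate in a minimum of two-thirds of the intervention". No separate rule is given for the waitlist arm.

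The same section describes the effect of the group as measured "relative to the wait-list control group (who will have only received the booklet intervention". Under Data collection procedures, Step 3, the waitlist takes the programme only after the comparison data are in: "The waitlist control group will then proceed to participate in the group intervention".

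The outcome reaches the two arms by different routes (same section). In the group arm, "participants will be provided with the follow up questionnaire as part of the last group session". For controls, "Participants in the waitlist control group will be completing the 6-month follow up assessment from baseline in Step 2". Under Data collection procedures, Step 2, six-month follow-up is planned for every Step 2 participant, with a prompt letter and then completion by phone, on paper or online.

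**The concern.** Two stated rules are at fault.

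**The intention-to-treat description.** Intention-to-treat analyses each randomised parent in the allocated arm, whatever was attended. It makes no assumption that anyone completed. Assuming completion cannot account for dropout, because an analysis of covariance needs a follow-up score and the assumption does not supply one. This matters more than usual here. The group-arm questionnaire is handed out at a session a parent may miss, while the waitlist questionnaire does not depend on attendance. The Intervention section itself warns of low participation and high attrition in face-to-face groups of this kind.

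**The per-protocol rule.** It conditions on something that can happen in only one arm before the outcome is measured. The parents kept in the group arm are then a selected subset, and the controls are not. If those who attend would have done better or worse anyway, the difference between arms mixes that selection with the effect of the group programme.

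At stake is the only randomised evidence in the study, on whether the group adds anything to the booklet.

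**Working it through.** The plan gives no attendance rate and no figure for this point, so there is nothing to reproduce. The check is a reading of the text followed by an illustration.

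**Step 1. Can the two-thirds rule be applied to both arms?** At the comparison, controls have had the booklet only, and they attend the group afterwards. Three readings are possible:

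| Reading | Consequence |
|---|---|
| Rule applied literally to both arms at the comparison | No control qualifies, so the control arm is empty |
| Rule applied to the group arm only | Selected attenders against all controls |
| Controls filtered on their later attendance | Controls selected on an event after their outcome, which that outcome may influence |

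Only the second can be carried out at the time of the comparison. None of the three preserves the randomised comparison.

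**Step 2. How large could the bias be under the second reading?**

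Inputs from the protocol article: 60 per arm, analysis of covariance on baseline, alpha 0.05.

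Inputs assumed, because the article gives none:
- no true group effect, outcome SD 1, complete outcomes;
- baseline to follow-up correlation ρ = 0.6;
- a share p of the group arm meeting the rule: 80%, 67% or 50%;
- a correlation r between propensity to attend and the part of the outcome not explained by baseline: 0, 0.2 or 0.4.

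The expected bias from filtering the group arm alone is

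bias = √(1 − ρ²) × r × φ(c)/p,

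where c is the normal cut-off that leaves a share p above it and φ is the normal density. With ρ = 0.6, √(1 − 0.36) = 0.8. For p = 0.5, c = 0 and φ(0)/0.5 = 0.399/0.5 = 0.798. With r = 0.4 the bias is 0.8 × 0.4 × 0.798 = 0.255 SD.

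Simulation, 4,000 runs per cell:

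| Share meeting rule | r | Filtered: bias (SD) | Filtered: type I error | By allocation: bias (SD) | By allocation: type I error |
|---|---|---|---|---|---|
| 80% | 0 | −0.002 | 0.050 | −0.002 | 0.050 |
| 80% | 0.2 | 0.052 | 0.060 | −0.005 | 0.047 |
| 80% | 0.4 | 0.108 | 0.111 | −0.002 | 0.054 |
| 67% | 0 | 0.000 | 0.046 | −0.001 | 0.049 |
| 67% | 0.2 | 0.085 | 0.079 | 0.001 | 0.048 |
| 67% | 0.4 | 0.177 | 0.190 | 0.002 | 0.051 |
| 50% | 0 | 0.004 | 0.059 | 0.002 | 0.054 |
| 50% | 0.2 | 0.125 | 0.108 | −0.002 | 0.054 |
| 50% | 0.4 | 0.254 | 0.293 | −0.001 | 0.045 |

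The last filtered cell (0.254) agrees with the formula (0.255). A negative r reverses the sign of the bias.

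**Step 3. What does this say about the intention-to-treat analysis?** With outcomes obtained for everyone, comparison by allocation shows no bias in any row and type I error of 0.045 to 0.054. The flaw is in how the analysis is described and in the attendance-linked route for collecting outcomes. The comparison by allocation itself is sound.

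**The case against.** The strongest defence is that the article names the intention-to-treat principle, covers everyone randomised and compares by allocation. The natural reading is analysis as allocated, loosely worded. Handling of missing data and the ranking of analysis sets are often left to a statistical analysis plan, which is not shown here. The six-month follow-up of all Step 2 participants could supply scores for group-arm parents who miss the last session. The per-protocol filter was probably meant for the group arm only, and selection is a familiar limit of any per-protocol analysis.

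Much of this stands. A reader might infer that neither Step 3 analysis gives a fair comparison. The document does not support that for intention-to-treat: by allocation, with outcomes obtained, it is fair. Nor does anything say that a claim would rest on whichever analysis reaches significance, and intention-to-treat is listed first. The absence of a missing-data method is not part of this point.

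Two things remain. The printed description of intention-to-treat is wrong, and the Step 3 text does not say that the six-month contact will be used for group-arm non-attenders. It assigns that assessment to the waitlist as the control data. The per-protocol rule is also more than an ordinary limitation, because it has no counterpart in the control arm at the comparison and the article does not say how controls are to be treated.

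**Conclusion.** The point holds in this form. Intention-to-treat is misdescribed, and the two-thirds rule cannot be met by waitlist parents at the comparison, so the per-protocol contrast is not randomised. It is biased if attendance is prognostic after baseline adjustment and unbiased if it is not.

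The document fixes neither size nor direction. The 0 to 0.25 SD range rests wholly on the assumed attendance shares and correlations. A reader might want to state the bias as a percentage of the planned effect, or to say that it favours the group. Neither is supported: no attendance rate or prognostic gap is given, and the hypothesised effect sizes of 0.5 and 0.3 can be read as a between-arm difference of 0.2 or of 0.5.

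**What to change.** In Statistical analyses, Step 3:

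1. Replace the intention-to-treat description with: the primary analysis compares all randomised parents in their allocated arm, regardless of attendance.
2. State that the follow-up questionnaire will also be sought from group-arm parents who miss the last session, using the six-month phone, mail or online contact already planned for all Step 2 participants.
3. Label the attendance-based analysis supportive. State that the two-thirds filter applies to the group arm alone and that the result is not a randomised comparison. Do not base the Step 3 conclusion on it.

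A complier-average estimate may be added, but only with its assumption stated that attendance below two-thirds has no effect. That assumption is open to doubt here, since the first week is a full-day session. A likelihood-based mixed model would not solve the dropout problem: with a single follow-up, parents who have only a baseline score add little to the contrast between arms.

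The cost is a few sentences, a few extra contacts within the existing procedure, and a somewhat smaller primary estimate, because non-attenders dilute it.

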## Discussion

CHiRP (Steps 1-3) aims to promote the psychological wellbeing and resilience of families of children and young people living with a chronic illness. This paper has provided an overview of the methodology to be employed to implement and evaluate a stepped care family resilience and wellbeing intervention.

The CHiRP intervention is guided by family resilience theory and identifies parents’ capacity to implement change to support optimal outcomes for the whole family. Utilising a behaviour change model (Padesky & Mooney 2012) parents will be encouraged to recognise family strengths, coping skills and resources and be provided with the opportunity to develop skills and knowledge that promote resilience.

The effectiveness of CHiRP will be measured using standardised, psychometrically validated instruments of relevant constructs, i.e. parental wellbeing, family functioning, family beliefs and social support, which collectively provide a measure of family resilience. Positive changes in outcome measures will indicate improved family wellbeing and resilience. Renzaho et al. (2013) have demonstrated a relationship between family functioning and parental psychological distress. It is expected that improvements in family functioning, including the dimensions of problem solving, communication, roles and behaviour will reflect adaptation and coping with chronic illness (Walsh 2002; McCubbin & McCubbin 1996) and will be associated with improved parental wellbeing. Changes on the family beliefs scales will reflect the process in resilience where families make meaning of adversity and maintain a positive outlook. Positive change on the social support measure will indicate improved perception of the availability of social support, a protective factor contributing to family resilience (Walsh 2002; Benzies & Mychasiuk 2009; McCubbin & McCubbin 1996). Analysis will also be able to contribute to the development of a psychometrically valid and reliable method for measuring family resilience.

CHiRP will employ a stepped care design to meet the demands of scientific rigour as well as conform to the pragmatic considerations involved in implementing research in a busy paediatric hospital setting. The dissemination of the Fact Sheet in Step 1, as part of routine paediatric discharge procedures, maximises the opportunity for families of hospitalised children (regardless of reason for admission) to receive brief, standardised information regarding ways to promote family resilience. The use of a single group pre-post design in Step 2, while potentially limiting the generalizability of outcomes for the booklet intervention, corresponds to the practicalities involved in implementing mental health promotion practices in the busy outpatient clinic environment (Merkel & Wright 2012). The use of a randomised waitlist control group in Step 3 ensures that the impact of the Information Support group can be rigorously evaluated, while allowing all consenting parents who are experiencing psychological distress to receive the highest level of intensity of the CHiRP intervention.

CHiRP meets an identified need for mental health promotion and prevention interventions that enhance family resilience and wellbeing in families of children with chronic illness who are more vulnerable to mental health issues. Through provision of the Family Resilience Fact Sheet and the Strong Parents, Resilient Families workbook, this study will provide information and strategies in a format that families can access and work through independently, without relying on intensive mental health or medical professional delivery. These family interventions are designed to empower parents to help the whole family cope better by learning new strategies and interacting with each other (Marsac et al. 2012). Further, through provision of the Information Support Group this study will provide additional support to parents reporting the highest levels of distress. If effective, CHiRP will increase the capacity of health services to provide standardised family resilience information and strategies to families living with a child with chronic illness.
